### Data management

Data collection will be done using digital forms. For any missing or inappropriate information the participant will be contacted on their cell phone number for correction and verification. Every effort will be made to complete the information. All study data will be stored on a protected central server at AKU. Only assigned members of the internal study team can access the respective files.

### Data analysis

We will use an intention-to-treat (ITT) analysis to evaluate changes in HbA1C and abnormal episodes of hypoglycemia and ketoacidosis. Generalized estimating equations will be used, with HbA1C readings at different points in time as our outcome variable. The mean change in HbA1C due to interventions will be estimated at 3 and 6 months, controlling for socio-demographic, clinical, nutritional, and physical activity variables. Secondary outcome variables are reported episodes of acute complications like hypoglycemia and diabetic ketoacidosis and will be recorded from interview-based data conducted at baseline and 3 and 6 months. In addition, these episodes will be further counted for the follow-up period using the daily log book of each participant.

Negative binomial regression will be used to observe the relationship among the four groups and number of episodes, adjusting for any socio-demographic, clinical, nutrition, and physical activity-related variables. If there is an excess number of ‘zeros’—meaning no abnormal episodes—then zero inflated negative binomial regression will be used instead of ordinary negative binomial regression. Twenty-four-hour dietary recall will be converted into total number of calories and percentage carbohydrate intake. Nutrition will be explored for total calories and food groups using factor analysis. Physical activity will be measured using step count data logged on a daily basis. These step counts will be used as time-dependent covariates for the final model. Step counts logged on a daily basis in two groups over a period of 6 months will be obtained from log books. The distribution of these data will be checked and, if needed, will be transformed. Changes in dietary habits and in step count over time will be used as a covariate in the final model. Physical activities reported during the three interviews will be converted into hours per week and categorized by type of activity as mild, moderate, and severe exercise.

In addition, we will explore blood glucose variability on a daily basis to calculate the average daily risk range for hypoglycemia using the standard method developed by Kovatchev and modified for relevant use by other investigators [15, 16].

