### Sample size and sampling technique

Overall, 120 patients with T1D will be randomized into four equal groups for evaluating changes in HbA1C using multiple measurements at multiple time points. Thirty patients in each group will be required in order to achieve 80% power for a two-sided level of significance of 5%, using a standard deviation of change in HbA1c between 1.1% and 2.3% and absolute difference of at least 2% expected over a period of 6 months within a group from baseline as well as when compared across the four groups [29]. A consecutive sampling technique will be used to enroll participants visiting AKU pediatric and endocrinology clinics and fulfilling the eligibility criteria.

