### Outcome measures

The major outcome variable is HbA1c, measured at baseline and 3 and 6 months. HbA1C will be compared with the control (routine) group and with the other groups in this factorial design. This will also be compared within one group: baseline to 3 months and baseline to 6 months. We will explore between-group variation and within-group variation and any interactions between the groups over time.

In addition, secondary outcome variables will be number of all hypoglycemic episodes (blood glucose < 70 mg/dL (3.9 mmol/L) and ketoacidosis episodes (hyperglycemia blood glucose > 11 mmol/L, venous pH < 7.3, or serum bicarbonate < 15 mmol/L, ketonemia blood ß-hydroxybuyrate ≥ 3 mmol/L), taken as a composite variable at baseline and 3 and 6 months [30–32]. Total number of abnormal episodes counted over the follow-up period will be considered as a composite outcome.

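### Baseline HbA1c reads as one of the GEE outcomes and is not named as an adjustment variable; if its group means are left free, the 3- and 6-month contrasts lose some precision

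*Protocol article*

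**What the plan says.** Outcome measures states: "The major outcome variable is HbA1c, measured at baseline and 3 and 6 months". It adds within-group comparisons: "This will also be compared within one group: baseline to 3 months and baseline to 6 months". It also plans to explore how the groups interact over time.

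Data analysis then fixes the model, "Generalized estimating equations will be used, with HbA1C readings at different points in time as our outcome variable", and its target: "The mean change in HbA1C due to interventions will be estimated at 3 and 6 months, controlling for socio-demographic, clinical, nutritional, and physical activity variables".

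Baseline HbA1c is not named in that adjustment list. Data collection tools describes the clinical information as age at onset, disease duration, complications, admissions, management habits and similar items, without HbA1c. Table 2 puts HbA1c under biochemical measures, a class that the adjustment list does not mention.

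On size, the sample size section says "Overall, 120 patients with T1D will be randomized into four equal groups". It assumes a difference of at least 2 percentage points over 6 months and a "standard deviation of change in HbA1c between 1.1% and 2.3"%, with 80% power at a two-sided 5% level.

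**The concern.** The baseline reading is taken before any intervention can act, so randomisation makes the expected group means equal at that visit. A model that still estimates a separate baseline mean for each group spends information on differences that are zero by design. The effect at 3 or 6 months then becomes follow-up minus baseline in one group against the same difference in another, and the random error of the baseline reading enters in full. With 30 patients per group, precision is worth having, and the value that would supply it is already collected.

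A second, smaller matter is missing visits. Follow-up HbA1c is tied to routine 3-monthly clinic visits (Follow-up and other procedures), so dropout related to poor control is plausible. Unweighted GEE on the available readings may then be biased, depending on the working correlation.

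**Working it through.** **Step 1. How baseline enters the model.** Outcome measures lists three readings as the outcome and asks for changes from baseline within groups and for interactions over time. Data analysis applies GEE to readings at different time points. A single model that delivers both within-group change and a group-by-time interaction most naturally has baseline as a level of time. The text does not say this outright, and it does not say whether group means are constrained equal at baseline.

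**Step 2. Reproduce the plan's own figure.** Inputs from the sample size section: difference 2, SD of change 2.3 (upper end), four groups, alpha 0.05 two-sided, power 0.80. For a one-way ANOVA F test on change scores with largest-minus-smallest mean difference 2:

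- f² = (2²/2)/4/2.3² = 0.5/5.29 = 0.0945
- noncentrality at 30 per group = 120 × 0.0945 = 11.3
- power = 0.803 at 30 per group, and 0.787 at 29

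So 30 per group reproduces, with no baseline adjustment.

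**Step 3. Variance with and without adjustment.** With equal SD s at both visits and correlation ρ:

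- change from baseline (free baseline means): 2s²(1 − ρ)
- adjusted for baseline: s²(1 − ρ²)
- ratio: (1 + ρ)/2

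**Step 4. Numbers.** The documents do not give ρ, so it is an assumed range. The residual SD is 2.3 × √((1 + ρ)/2).

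| Assumed ρ | Variance ratio | SE ratio | Residual SD | n per group for 80% | Power at 30 per group |
|---|---|---|---|---|---|
| no adjustment | 1 | 1 | 2.30 | 30 | 0.80 |
| 0.5 | 0.75 | 0.866 | 1.99 | 23 | 0.91 |
| 0.7 | 0.85 | 0.922 | 2.12 | 26 | 0.87 |
| 0.9 | 0.95 | 0.975 | 2.24 | 29 | 0.82 |

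**Step 5. Check by simulation.** Two arms of 30, three visits, 400 runs per setting, no missing data. Empirical standard error of the 6-month effect:

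| ρ | Baseline as outcome, free means | Baseline as covariate | Baseline as outcome, common mean |
|---|---|---|---|
| 0.5 | 0.600 | 0.507 | 0.506 |
| 0.7 | 0.592 | 0.554 | 0.555 |

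The loss comes from the free baseline means. Keeping baseline as an outcome costs nothing once its mean is common to all groups.

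**Step 6. Missing visits.** Same set-up, true effect −1.0, with 6-month dropout depending on the 3-month value differently by arm. Mean estimates at ρ = 0.5 and 0.7:

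- baseline as outcome, free means, independence working correlation: −1.32 and −1.56
- the same model with exchangeable working correlation, which was the true structure here: −1.06 and −1.05
- baseline as covariate, independence: −1.16 and −1.21

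These bias sizes depend on the assumed dropout mechanism and are illustrative only.

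**The case against.** The strongest reply is that the defect is inferred. The key sentence does not say that baseline is in the response, and the phrase "controlling for socio-demographic, clinical, nutritional, and physical activity variables" could be stretched to cover baseline HbA1c under its clinical heading. Whether baseline means are constrained is a detail that an analysis plan could settle, and a change-score analysis matches the basis on which the trial was sized. It stands that the reading is an inference. The stretch is less convincing, because the protocol's own description of clinical information omits HbA1c and Table 2 files it elsewhere. The article does fix the estimator, the response and the adjustment classes, so the point concerns what is written.

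Four stronger readings are tempting and are not supported.

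- **That the trial is underpowered.** It is not on this ground: the stated size reproduces without adjustment.
- **That the effect is diluted by averaging over three readings.** Data analysis estimates the effect at 3 and 6 months separately.
- **That the gain can be fixed from the document's SDs.** A reader might combine the 2.60 and 2.33 quoted in Rationale for inaccurate record-keepers with the SD of change of 2.3, giving r = (2.60² + 2.33² − 2.3²)/(2 × 2.60 × 2.33) = 0.57 and a saving above 25%. These figures come from different cited sources. The same recipe with SD of change 1.1 gives r = 0.91. For the accurate record-keepers (2.61 and 0.84, with 1.1) it gives 1.44, which is impossible.
- **That GEE always needs data missing completely at random.** Missingness that depends on modelled covariates is allowed, weighting or multiple imputation is valid under missing at random, and a correct working correlation removed most of the bias in Step 6. The protocol rules out none of these, gives no dropout rate and plans phone contact to complete missing information. The method for missing data is commonly left to the analysis plan, so its absence is no error.

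**Conclusion.** The point holds as a modest, free efficiency gain. On the natural reading of the two sections, baseline HbA1c is an outcome reading and not an adjustment variable. With free group means at baseline, the variance of the 3- and 6-month contrasts is then higher than it need be. Adjustment would cut it by 25%, 15% or 5% at an assumed correlation of 0.5, 0.7 or 0.9. This rests on equal SDs at baseline and follow-up and on a correlation that the documents do not give. If the sponsor already intends a baseline covariate or a common baseline mean, only the wording needs to say so.

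The missing-data point is secondary. Bias is possible under unweighted GEE with an independence working correlation when dropout depends on earlier HbA1c, but its size in this trial cannot be judged from the documents.

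**What to change.** In Data analysis, state one of two equivalent forms:

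- model the 3- and 6-month HbA1c readings as outcomes, with baseline HbA1c and its interaction with visit as covariates; or
- keep all three readings as outcomes, with one common baseline mean across the four groups. This form also yields the within-group changes from baseline that Outcome measures asks for.

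Report the group contrast at 6 months. A repeated-measures likelihood model with unstructured covariance is a reasonable choice for either form, since it handles missing visits under missing at random. If GEE is kept, name the working correlation and the missing-data assumption.

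The cost is a change of analysis wording. The baseline value is already measured, and neither the sample size nor the visit schedule changes.

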## Methods/design

### Study design

A factorial design will help to study lifestyle changes for self-management of T1D (Fig. 1). A randomized controlled method will enroll patients in a predefined sequence, assigning them in four groups. All groups will be working with a newly designed standard log book for documenting records for blood sugar and routine insulin dosage and care as provided by doctors, nurses, and nutritionists. The first group will all receive routine care follow-up, the second group will receive an additional e-device for measuring step count (fit bit), the third group will receive routine care and e-messages as reminders to maintain a daily log book, and the fourth group will receive an e-device for measuring step count (fit bit) and e-messages about maintaining the log book, blood glucose levels, and step count in addition to routine care. All groups will be followed up overall for a period of 6 months. HbA1c as a main outcome will be measured at least three times, at baseline, and then once every 3 months.

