### Data collection tools

At baseline we will determine the socio-demographic profile of patients, along with user satisfaction of maintaining log books and using the e-device for measuring step count. Additionally, clinical information for T1D and other co-morbidities, including age of onset, duration, complications, hospitalizations, habits for managing T1D, and other lifestyle characteristics, will be ascertained.

Two other tools will supplement data collection at baseline (0 months) and 3- and 6-month visits; namely, a 24-hour dietary recall [33] and physical activity assessment using both the International Physical Activity Questionnaire (IPAQ) and Youth Physical Activity Questionnaire (YPAQ) [34] (Table 2). The designed questionnaires and tools will be modified for clarity and cultural relevance after pilot testing on at least five T1D patients prior to initiation of the study. All groups will be followed up overall for a total period of 6 months. During these 6 months data for any additional clinic/hospital visit will be obtained from the medical record files of participants.

**Table 2 Tab2:** Assessments that will be carried out in the study and data collection time points (baseline, 3 months, and 6 months)

Variable	Component	Measurement tools/questions	Baseline	3 month	6 month
Socio-demographic measures		Age, Sex, Weight, Height, Marital Status, Education, Occupation and Parents Education, Occupation and Family history of diabetes	✓		
Health Related Information		History of Diabetes and History if comorbidities	✓		
		Episodes of complications, any hospital admission, Frequency of self-monitoring of blood glucose, frequency of maintaining log book	✓	✓	✓
Behavioral Measure		Frequency of visit to diabetic clinic, frequency of visit to dietitian	✓	✓	✓
	Daily Physical activity of 1 week	Questionnaire adapted from IPAQ and YPAQ	✓	✓	✓
	Barriers to physical activity	Questionnaire adapted from IPAQ and YPAQ	✓	✓	✓
	Dietary Intake	Self-Reported 24- Hour Dietary Recall Questionnaire	✓	✓	✓
Biochemical measures	Pathology	HbA1C	✓	✓	✓

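### The acute-episode count draws on two overlapping sources, names neither as the one to be modelled, and one of them is expected to record more completely in the e-message arms

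*Protocol article*

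**What the plan says.** Outcome measures in the protocol article describes the acute-complication outcome in two ways. Episodes of hypoglycaemia (glucose below 70 mg/dL) and ketoacidosis are "taken as a composite variable at baseline and 3 and 6 months". The same section then says: "Total number of abnormal episodes counted over the follow-up period will be considered as a composite outcome".

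Data analysis gives two sources. Reported episodes "will be recorded from interview-based data conducted at baseline and 3 and 6 months". The next sentence is: "In addition, these episodes will be further counted for the follow-up period using the daily log book of each participant".

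The model follows: "Negative binomial regression will be used to observe the relationship among the four groups and number of episodes". A zero-inflated version is the fallback. Adjustment is allowed for any variables of several broad kinds, clinical ones included. No offset or person-time term is mentioned.

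Table 2, under Data collection tools, has one row for "Episodes of complications, any hospital admission, Frequency of self-monitoring of blood glucose, frequency of maintaining log book", ticked at baseline, 3 and 6 months, with no recall period. On duration, Study design says: "All groups will be followed up overall for a period of 6 months".

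Two other places bear on this. Randomization and Table 1 show that groups C and D receive reminders, some of which prompt patients to check and record their glucose. The Discussion states the hypothesis that log-book keeping will rise substantially in those who receive reminders.

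**The concern.** Comparing acute complications across the groups is a named secondary objective. The model needs one number per patient, and the plan leaves open whether that number comes from the interviews, the log book, the sum of both, or the distinct episodes found in either. These are different outcomes and can give different answers.

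The choice would matter less if the log book captured the same share of episodes in every arm. The trial expects that it will not. A hypoglycaemic episode is a glucose value below a threshold, so it enters the log book only if the patient tests and writes the value down. The e-messages are meant to increase that behaviour. If they work as hypothesised, the messaged arms will show more logged episodes even when the true rates are equal. A real reduction could be hidden, or a harmless intervention could look harmful.

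Because the source is open, the result can also depend on a counting rule settled after the data are seen.

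**Working it through.** The protocol gives no episode rate, capture rate or dropout rate, so there is no stated figure to reproduce. The check shows how far the between-arm ratio depends on the counting rule.

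**Assumed inputs.** The true episode rates are equal. Interview capture is *i* = 0.60 in both arms. Log-book capture is *l*₀ in an arm without messages and *l*₁ in an arm with messages. The two sources capture episodes independently.

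**Expected share of true episodes counted, by rule**

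- Sum of both sources: *i* + *l*
- Distinct episodes, de-duplicated: 1 − (1 − *i*)(1 − *l*)
- Log book alone: *l*
- Interview alone: *i*

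**Central case, *l*₀ = 0.40 and *l*₁ = 0.80**

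- Sum: (0.60 + 0.80)/(0.60 + 0.40) = 1.40/1.00 = 1.40
- De-duplicated: (1 − 0.40 × 0.20)/(1 − 0.40 × 0.60) = 0.92/0.76 = 1.21
- Log book alone: 0.80/0.40 = 2.00
- Interview alone: 0.60/0.60 = 1.00

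**Range**

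| Log-book capture, without vs with messages | Sum | De-duplicated | Log book alone | Interview alone |
|---|---|---|---|---|
| 60% vs 60% | 1.00 | 1.00 | 1.00 | 1.00 |
| 50% vs 70% | 1.18 | 1.10 | 1.40 | 1.00 |
| 40% vs 80% | 1.40 | 1.21 | 2.00 | 1.00 |
| 30% vs 90% | 1.67 | 1.33 | 3.00 | 1.00 |

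Three things follow.

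1. Double-counting alone does not bias the comparison. At 60% capture by each source in both arms, the sum exceeds the distinct episodes by a factor of 1.20/0.84 = 1.43, but the arm ratio stays at 1.00.
2. Bias comes from unequal log-book capture. Summing makes it worse than de-duplicating does, but de-duplication does not remove it.
3. In the central case, a true rate ratio of 1/1.40 = 0.71 would appear as no difference under summing, and 0.76/0.92 = 0.83 would do so after de-duplication.

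**Exposure.** Without an offset, the ratio of expected totals is the true rate ratio multiplied by the ratio of mean observed time in the two arms. That factor is 1 when observed time is equal on average. The protocol gives nothing from which to size any departure.

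**Baseline.** The study log book is issued at enrolment, so a baseline count can come only from the interview. It has no stated window, and it is listed in the same phrase as the 3- and 6-month values of the composite.

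**The case against.** The strongest reply is that the text may describe two separate measures. Outcome measures gives a composite at three visits and then, in its own sentence, a total over follow-up. Data analysis follows the same order: interviews at three visits, then the log book for the follow-up period. On that reading the interview feeds the first measure and the log book the second, and nothing is added together. This is fair. A reader might infer that every episode both remembered and logged is certain to be counted twice, and no sentence says so. The reply still leaves the modelled count unnamed. If the total is the log-book count, it rests on the source with the largest arm-related distortion in the table.

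A second reply is that offsets, partial follow-up and questionnaire wording commonly sit in an analysis plan or full protocol that is not shown. That stands for the offset and the baseline window taken alone, so they are supporting points here. It does not cover the source of an outcome that the protocol itself sets out to define.

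Some stronger readings are tempting, and the document does not support them:

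- *Follow-up is of unequal length.* Six months is fixed for all groups, and no dropout rate or arm difference in dropout is stated.
- *Medical records are a third source of the count.* The text says only: "During these 6 months data for any additional clinic/hospital visit will be obtained from the medical record files of participants". It does not say that these data enter the episode total.
- *The baseline count is unusable, or the best adjuster has been lost.* The count is collected, a window may be in the questionnaire, and any clinical variable may be adjusted for. Leaving a baseline covariate out of a randomised comparison costs precision and does not cause bias.

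**Conclusion.** The point holds as a badly fixed secondary outcome. The modelled number of episodes has two overlapping sources, no named primary source, no rule for counting an episode once, and no exposure term. By the trial's own hypothesis, one source is expected to record more completely in the messaged arms.

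Under the assumed 40% against 80% log-book capture and no true difference, the apparent ratio runs from 1.00 to 2.00 depending only on the counting rule. With 50% against 70% it runs from 1.00 to 1.40. These figures rest on assumed capture rates, independence of the two sources, and interview capture that is equal across arms. The last is the weakest assumption. Patients who test and log more may also have more to report at interview, so interview capture is less driven by the messages but not free of them.

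The direction is clearer than the size: differential logging pushes counts up in the messaged arms. HbA1c, the main outcome, is measured in the laboratory and is not affected.

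**What to change.** In Outcome measures and Data analysis:

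1. Name one primary source for the modelled count. The interview is preferable, asked in identical words in all four arms, because its capture is less driven by the messages.
2. State that each episode is counted once, and that the two counts are not added.
3. Report the log-book count separately as a supporting analysis, with days of log-book entries as the exposure. This allows for unequal record keeping by day, but not for more tests on a logged day.
4. Model a rate by including log(observed time) as an offset in the negative binomial model and in its zero-inflated fallback.
5. Ask the baseline question over a stated fixed window that matches the one used at the follow-up interviews. Use that count as a covariate and not as part of the outcome.

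The cost is a few sentences of protocol text and one changed baseline question, with no new visits. There are two downsides. Interview recall misses mild episodes, so the primary count will be lower than the true number. Recruitment began in October 2018, so patients already enrolled may lack the fixed-window baseline value, and the plan should say how that gap is handled. The source should be fixed before any comparison by arm is seen.

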### Inclusion and exclusion criteria

Males and females diagnosed with T1D and aged more than 14 years who present to pediatric and endocrine clinics of AKU and have a smart phone or a family member with a smart phone, such as parents or elder sibling, are eligible to participate in the study. However, patients using an “insulin pump” will be excluded. Patients with complicated health conditions such as neurodevelopmental delay and thalassemia will be excluded. Furthermore, patients already using any kind of authentic e-device for measuring step count and/or physical activity will also be excluded from the study.

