**Fig. 2 Fig2:**
[figure not shown]
Logbooks for groups A and C to record their daily blood sugar readings and insulin doses and for groups B and D to record daily blood sugar readings, insulin doses, and step count

**Table 1 Tab1:** Mobile messages by group

E-MESSEGES FOR GROUP C	E-MESSEGES FOR GROUP D
Remember to check your blood sugars before every meal and record it in your logbook. Keep up the good work.	How many steps have you taken today? Make sure your fitbit is charged to record all that hard work! Good luck and have a healthy day
Don’t forget to check and record your blood sugar and insulin dose in your logbook. This record will help you to discuss it with your doctor and make your sugar levels near to the targets. Have a good day!	Recording your step count can help you to manage your blood sugar, so Fitbit is here to help you to count your steps daily. Don’t forget to charge it. Have a good day!
Keeping an eye on your blood sugar. Knowing this can help you and your doctor to adjust your food choices and insulin doses accordingly. Thanks for checking and recording it in your log book!	Remember! Any type of physical activity you do will help you lower your blood glucose! It’s time to go for a walk and increase your daily steps. Fitbit is here to count your every step so don’t forget to note your steps daily in your logbook. Thank you for all your hard work!
Self-testing of your blood sugar is an important tool in managing your treatment plan and preventing diabetes complications, so try to keep your blood sugar levels record in your logbook as suggested by your physician and help yourself and your doctor to manage your treatment accordingly.	Fitbit is with you to count your steps during housework, outdoor work, job activities, recreational activities, and exercise. So charge you fitbit as required and don’t forget to record your steps daily in logbook. Thanks
Self-monitoring of blood sugar levels provides useful information for diabetes management as it can help you reach your overall treatment goals. So keep checking and recording it in your logbook. Good day!	Improved fitness lowers your blood glucose level, relieves stress, helps insulin work better and strengthens the heart, muscles, and bones. It’s time to set your goals and make your life healthier. Wear your fitbit device all the day and record your steps in log book. Don’t forget to charge it. Stay Healthy!

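### The planned models adjust for step counts and dietary change that arise after randomisation, and step counts exist in only two of the four groups, so the device coefficient is not the intention-to-treat effect

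*Protocol article*

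**What the plan says.** The first paragraph of the Data analysis section commits to intention to treat. It estimates the mean HbA1c change due to the interventions at 3 and 6 months by generalized estimating equations (GEE), "controlling for socio-demographic, clinical, nutritional, and physical activity variables". The second paragraph opens with negative binomial regression for hypoglycaemia and ketoacidosis episodes, with a parallel adjustment for nutrition and physical activity. It then defines the activity variable, "Physical activity will be measured using step count data logged on a daily basis", and gives its role: "These step counts will be used as time-dependent covariates for the final model". It adds: "Changes in dietary habits and in step count over time will be used as a covariate in the final model".

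The same paragraph limits where steps exist: "Step counts logged on a daily basis in two groups over a period of 6 months will be obtained from log books". The Fig. 2 caption names the groups. The log books of A and C hold blood sugar and insulin dose; the fuller version is "for groups B and D to record daily blood sugar readings, insulin doses, and step count".

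Both primary objectives (Study objectives) are comparisons with routine clinical care.

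**The concern.** An intention-to-treat estimate compares groups as randomised. Steps taken after allocation are a consequence of allocation: the device exists to count them, and a group D message in Table 1 tells patients to "go for a walk and increase your daily steps". Conditioning on them asks what the device does at a fixed number of steps, which is a different question from what assigning the device does.

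There is also a data problem. The covariate is recorded only in the groups that received the device. A four-group model containing it must either lose the other two groups or be given values that nobody measured. At stake is the second primary objective, device versus routine care.

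**Working it through.** The plan gives no figure on this point to reproduce. The check uses its design and its stated covariates.

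**Inputs from the protocol**
- 30 patients per group, 120 in total, and a difference of 2 percentage points (Sample size and sampling technique).
- Steps logged in B and D only (Data analysis; Fig. 2 caption).
- No other step source is planned for A and C, and none before randomisation for anyone: "patients already using any kind of authentic e-device for measuring step count and/or physical activity will also be excluded from the study" (Inclusion and exclusion criteria).

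**Assumed, because the documents give no values**
- Total device effect T = -2.0, taking the planned difference for illustration.
- Share m of that effect running through steps: 25% to 100%.
- Mean daily steps of 6,000 without the device and 8,000 with it.
- Steps otherwise unconfounded with HbA1c.

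**Does the final model include the HbA1c model?** The phrase stands in the paragraph that opens with the episode model. The GEE sentence, however, also controls for physical activity, and the only definition given for the adjustment variable is step count. Including the HbA1c model is therefore an inference, but a sound one. On either reading, a four-group model receives a covariate that two groups lack.

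**Case 1: complete cases**
- Patients with steps: 30 + 30 = 60 of 120, all with the device.
- Columns of the model: intercept, device, message, steps. Among B and D the device column equals the intercept, so the rank is 3 of 4 and the device effect cannot be estimated.
- What remains is D versus B. Its standard error relative to a 60 v 60 message comparison is √(2/30) / √(2/60) = √2 = 1.41.

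**Case 2: plausible steps filled in for A and C**
- Device coefficient = T × (1 - m).

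**Case 3: steps set to zero in A and C**
- Slope per 1,000 steps: b = T × m / (8 - 6) = T × m / 2.
- The device-group mean is extrapolated back to zero steps, so the device coefficient = T - 8b = T × (1 - 4m).

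| m | Total effect | Case 2 | Case 3 |
|---|---|---|---|
| 25% | -2.0 | -1.5 | 0.0 |
| 50% | -2.0 | -1.0 | +2.0 |
| 75% | -2.0 | -0.5 | +4.0 |
| 100% | -2.0 | 0.0 | +6.0 |

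A large simulated 2×2 trial under these assumptions gave the same values. It used linear regression, whose mean model is that of a GEE with identity link. Without steps in the model it returned -2.0 in every row.

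**The case against.** The best defence is that an analysis of steps has a proper purpose. The Discussion expects step count to correlate with glucose and to interact with the messages, and the Outcome measures section separately plans between-group HbA1c comparisons. The final model could then be a supplementary one. Coding also matters: centring steps within the device groups and setting the others to zero kept the total effect at -2.0 in the simulation, and such coding is commonly left to an analysis plan.

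Part of this stands. A step analysis belongs in the trial, and a harmless coding exists. But the Data analysis section plans no such coding and names no model without these covariates as primary. The problem is a stated choice of covariates, not an omitted detail. Nor does the activity questionnaire, which all groups complete, rescue the plan: the text does not put it in place of steps, and its 3- and 6-month values would also arise after randomisation.

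A reader might infer more than the documents support:
- **That the device effect is wholly adjusted away and the control group is lost as well.** These are alternatives, depending on how absent steps are handled. Complete removal in Case 2 needs m = 100%.
- **That the estimate must shrink towards zero.** Case 3 shows it can change sign.
- **That the message effect (the first primary objective) is biased.** The group C messages in Table 1 concern checking and recording glucose; none mentions steps, and one mentions food choices in passing. The group D messages do urge walking, but the documents give nothing from which to size a bias, and the simulation gave messages no effect on steps.
- **That GEE is biased through its working correlation.** The protocol names no working correlation and does not describe earlier HbA1c driving later steps.

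**Conclusion.** The point holds in this form. The protocol promises intention to treat but adjusts its models for post-randomisation steps and dietary change, and steps are available for only 60 of 120 planned patients. With complete cases, device versus routine care cannot be estimated. With steps filled in, the device coefficient is the total effect times (1 - m), and with zeros filled in it is arbitrary. In none of these cases is it the intention-to-treat effect.

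The count of 60 and the loss of rank follow from the documents alone. The sizes in Cases 2 and 3 are illustrations that rest on assumed shares and step counts. Application to the HbA1c model is inferred from the GEE sentence, as set out above. Because following the text gives either no answer or a different answer to a primary objective, it should be corrected before the analysis.

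**What to change.** - **Primary HbA1c GEE and episode model:** use randomised group (or the two factors and their interaction), time where applicable, and baseline covariates only.
- **Baseline HbA1c:** if it is a covariate, only the 3- and 6-month values are outcomes. Otherwise keep all three readings as outcomes with group-by-time terms.
- **Adjustment clauses:** limit both the GEE clause and the negative binomial clause to baseline values of nutrition and physical activity. Baseline activity would come from the IPAQ/YPAQ questionnaires, since no baseline step count is planned.
- **Final-model sentences:** remove the two sentences that enter step counts and changes in diet and steps from the primary and episode models. Deleting them alone is not enough, because the two adjustment clauses would remain.
- **Step count:** report it against glucose and HbA1c as an exploratory, non-randomised analysis within B and D. For any four-group mediation analysis, use IPAQ/YPAQ, which all groups complete at 0, 3 and 6 months.

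The cost is a few sentences of analysis wording, with no new data or patients. All 120 planned patients stay in the comparison. At 30 per group, device versus routine care has 92% power for a difference of 2 at the larger planned SD of 2.3: 2 / (2.3 × √(2/30)) = 3.37, and 3.37 - 1.96 = 1.41.
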